### Schedule of trial activities

2.3.

Figure 1 shows a simplified schematic of study flow from screening to termination, including the open-label phase for participants who have been randomized to placebo and unblinded.

**Figure 1 fig1:**
[figure not shown]
Simplified study flow diagram.

#### Recruitment

2.3.1.

The Yale OCD Research Clinic sees a large number of potential participants with OCD annually. Recruitment strategies include community referrals (e.g., other institutional clinics/departments, local private practices, local advocacy groups or grassroots organizations) and self-referrals (e.g., through the clinic’s website, in response to online/radio/cable/TV ads or community flyers). Potential participants may also reach out through contact information provided on this study’s ClinicalTrials.gov page.

#### Pre-screening, informed consent, and screening

2.3.2.

Potential participants who express interest in this study will be directed to study personnel for phone pre-screening, informed consent, and other screening procedures. While most of these procedures/visits will be conducted in-person, some can be conducted remotely/virtually due to state/federal or site-specific COVID-19 restrictions, or because of distance.

First, potential participants will be scheduled to complete a phone pre-screen with a research assistant to review demographics, medical and psychiatric history, and screening for presence of metal implants in their body (for MRI safety). Information from this screen will be entered synchronously by study personnel directly into an electronic source document, and reviewed by the principal investigator (PI) to ascertain preliminary eligibility.

Next, participants deemed eligible at this step will then be invited for an in-person informed consent visit with the PI and/or appropriate study team members. All study procedures will be described in detail and an IRB-approved informed consent document will be reviewed and signed.

After obtaining informed consent, trained study personnel will meet with participants to complete a comprehensive psychiatric evaluation comprising a psychosocial interview, the Mini International Neuropsychiatric Interview, Version 7.0.2 (MINI-7.0.2) (48), the Y-BOCS (36, 37), the Lifetime version of the Columbia-Suicide Severity Rating Scale (C-SSRS) (47), and the obsessive–compulsive personality disorder (OCPD) and borderline personality disorder (BPD) modules from the Structured Clinical Interview for DSM-IV Personality Disorders (SCID-II) (49). In this psychiatric evaluation visit, participants were also inquired in detail about any known formal psychiatric diagnoses among immediate family members.

Participants will also complete a separate, in-person medical evaluation visit with the PI or study physician. This will comprise a medical examination, blood draws, urinary drug and pregnancy screens (if of childbearing potential), liver and thyroid function tests, and electrocardiogram (ECG). Participants will be reminded that these results will be documented on a medical chart created for them, and that they are free to discontinue participation at any time.

Inclusion criteria are:

Primary DSM-5 diagnosis of OCDY-BOCS score of 19 or greaterFailure of at least one trial of standard care treatment (medication and/or psychotherapy [CBT/ERP]) for OCDEnglish proficiency and fluency, and ability to understand the consent process and provide written informed consentWillingness to sign a medical release for direct communication between research staff and external provider(s) about the participant’s treatment and medical historiesNon-consumption of SSRIs for at least 8 weeks at the time of randomization^1^Willingness to refrain from psychiatric medications (e.g., antidepressants, first- and second-generation antipsychotics, mood stabilizers) during the study period, as well as certain other medications (e.g., anti-seizure medications, cardiovascular medications, and aldomet specifically) during the day of dosing^2^Willingness to abstain from THC-containing products for study duration. A negative urinary drug screen is also required at baseline and the day of dosing.A negative urinary pregnancy screen at study entry and day of dosing if of childbearing potential, and willingness to use adequate birth control for study durationHaving a contact person who is willing and able to be reached by the study team in the event of an emergency/crisis, and who is able to transport the participant home at the end of the inpatient stay/dosing weekWillingness to commit to all study procedures and visits, including inpatient stay, assessments and self-reports, neuroimaging, and being medically cleared to be discharged and transported home at the end of the dosing week

Exclusion criteria are:

Personal or immediate family history of schizophrenia spectrum and other psychotic disorders, bipolar I or II disorder, or major depressive disorder with psychotic featuresActive suicidal intentUnremitted Tourette syndromeAutism spectrum disorderOCPD or BPDCurrent substance use disorder (except mild alcohol use disorder)Unstable neurological or medical condition(s) that may render study procedures unsafe, including poorly managed diabetes, hypertension, or cardiovascular conditions, or history of seizure(s) or chronic/severe headachesAny history of head injury with loss of consciousness for more than 30 minAny contraindications to undergoing an MRI scan, including having metal implants or metal fragments in the bodyAny use of psychedelic substances within the prior 12 months

#### Enrollment confirmation and randomization

2.3.3.

The PI will confirm participants’ enrollment *via* phone call and/or email after they have been reviewed successfully for all eligibility criteria. The study pharmacist alone will generate and maintain the block randomization sequence (i.e., equal number of participants in each treatment condition) using an online program to ensure blinding.

#### Blinding

2.3.4.

The following additional procedures will be undertaken to maintain blinding in this study. Participants and all research team members (including study facilitators and independent raters) will be kept blind to condition allocation before, during, and for an interval following dosing (see section 2.3.8). Psilocybin and niacin capsules are identical in terms of color, taste, and smell. Niacin (at our elected dosage of 250 mg) may also induce mild psychological (e.g., anxiety) and physiological effects (e.g., hot flushes, tingling sensations, increased heart rate) similar too low to moderate doses of psilocybin. In spite of these measures, blinding and placebo control remain a distinct challenge in psilocybin (and other psychedelic) studies due to the unique effects of psilocybin. As such, study facilitators will be attentive to and document participants’ report in regards to perceived study drug allocation anytime during dosing, up to the point of unblinding. In the event of a serious, possibly drug-related AE in which knowledge of study drug allocation is required for emergency intervention, the PI, study physician, or external emergency personnel will contact the study pharmacist. In these situations, the blind may be broken to whomever is necessary to ensure participants’ safety. The exception is the assigned independent rater, who will remain blind to allocation even under these circumstances.

#### Preparation

2.3.5.

For brevity, essential procedures for preparatory, dosing, and integration sessions in the randomized phase are concisely described from here onwards. Detailed procedures for study team members serving as study facilitators for these visits are described in a separate manual (50). While facilitator pairing will likely differ from participant to participant, the same pair of facilitators will work with each participant until study participation is completed.

During the two pre-dosing preparatory sessions, participants will meet with their assigned pair of study facilitators trained to discuss their experiences with OCD and the impact on their quality of life and functioning, life goals and aspirations, significant past experiences, and their specific hopes, expectations, fears, goals, etc. for the upcoming dosing session. In these sessions, facilitators provide psychoeducation on possible acute effects of psilocybin, and ways to ground oneself from challenging drug effects (e.g., maintaining curiosity and openness, taking the headphones and eye shades off, deep breathing, reminding participants that challenging drug effects are temporary). Further, facilitators will collaborate with participants to establish consensual boundaries around therapeutic, non-sexual touch prior to the dosing session (e.g., typically, holding the participant’s hand, or placing a hand on their arm or shoulder). Lastly, facilitators will collaborate with participants to adjust aspects of the physical setting (e.g., location of furniture, type of hanging art) to ensure physical and aesthetic comfort for the dosing day itself. At the end of the preparatory sessions, facilitators should have collaborated with participants to cultivate a presumably conducive psychological state (i.e., set) (51) for the upcoming dosing session.

#### Neuroimaging

2.3.6.

In the randomized phase, neuroimaging will be conducted at baseline 24 h pre-dosing and 48 h post-dosing. At these intervals, study personnel will accompany participants to the MRRC, where technologists will review participants’ responses on the MRI Safety Questionnaire, obtain signed informed consent for the day’s neuroimaging procedures, and conduct additional screening and safety determination if necessary (e.g., X-ray to rule out embedded metal in case of recent exposure).

MRI acquisition will be conducted using a Siemens 3 Tesla MRI scanner. Using a 64-channel head coil, the scan protocol will begin with a 3-plane localizer, scout image, and aligned 3-plane localizer that will serve as a localization series for the other acquisitions. The remaining multimodal MR pulse sequences will include: high resolution T1-weighted imaging (i.e., MPRAGE); high resolution T2-weighted imaging; spin echo field maps acquired in opposing phase encoding directions prior to each fMRI session; multi-band BOLD gradient echo planar imaging at rest; diffusion weighted imaging (DWI), and arterial spin labeling (ASL). The T1 and T2 acquisitions are set to use an “Adjust Volume” that matches the size and positioning of the spin echo field maps and resting state fMRI scans. Total MR acquisition may last between 1.5 and 2 h depending on whether some series must be re-acquired due to confounds/artifacts.

#### Dosing

2.3.7.

Early in the morning of the dosing day (approximately 7 am), participants will be allowed to consume a light breakfast free of milk/dairy or caffeine, so as to not affect drug absorption or effects. By approximately 10 am, the participant will be settled into a study treatment room on the CNRU, accompanied by the study facilitators, to begin the dosing session. One facilitator will be designated beforehand to monitor the participant’s vitals (blood pressure, heart rate, temperature) and subjective units of distress (SUDS; from 0 to 100) at baseline prior to ingestion of the drug capsule, as well as at subsequent intervals until the end of the dosing session (i.e., 15 and 30 min post-dosing, then every 30 min after until 2 h post-dosing, then every hour after until end of dosing session). Vital sign monitoring will continue beyond the dosing session at regularly scheduled CNRU shift checks for the remainder of the inpatient stay.

The study pharmacist will prepare and deliver the study drug by 10 am, and remain in the room until the participant has ingested the study drug. During the first few hours, participants will be encouraged to lie comfortably in bed with the headphones and eye shades on, and listen to a standardized music playlist designed to mimic the prototypical arc of a psilocybin experience. The music helps eliminate extraneous distractions and facilitate “dropping into” the dosing experience. While there are likely idiosyncrasies to each psilocybin experience, most follow a trajectory of ‘ascent’ (0 to 1.5 h post-dosing; onset of drug effects), ‘peak’ (1.5 to 3.5 h post-dosing; greatest intensity of drug effects, sometimes in one or more ‘waves’), and ‘descent’ (3.5 to 5 h and beyond; subsiding of acute drug effects).

Regardless of condition assignment, study facilitators will attend to participants’ physical and psychological needs and safety for the entire dosing session (50). Specifically, facilitators will attend to participants’ reactions to any arising internal experiences, as well as support them in engaging openly with these experiences in a non-directive, non-judgmental, compassionate, and empathetic manner. At least one facilitator must be physically present in the room with the participant at all times. If appropriate, facilitators will employ grounding strategies and/or consensually agreed therapeutic touch to alleviate participants’ distress. In the event that participants do not respond to these strategies and/or if participants are endangering themselves or others, the PI/study physician will prescribe and administer a one-time anxiolytic “rescue” medication (benzodiazepine) or intervene otherwise as appropriate.

The dosing session is expected to last up to 6 or more hours. Participants will be required to stay in the dosing room for at least 4 h, or until the effects of the ingested drug have worn off, whichever is longer. At the end of the session, participants will be asked about any residual drug effects or other AEs. Each participant will be expected to remain under observation in the dosing room until the participant, study facilitators, and PI/study physician all agree that the participant’s perception, cognition, functioning, and judgment have returned to their baseline levels or are no longer significantly impaired by the drug. Participants will be encouraged to document in any mode of creative expression their recollection and initial reflections of their dosing experience prior to the first integration session 48 h post-dosing. This may offer participants the opportunity to independently consolidate any emerging insights, and provide content to explore during integration sessions. Participants were also discouraged from discussing their dosing experience at length with family or friends over the phone, or in-person with staff or other patients on the unit, and to reserve such discussion for the integration sessions. Thereafter, participants will be allowed to have dinner and retire to their room on the unit.

If participants experience or report any persisting drug effects or SAEs, including acute suicidality, they will continue to be monitored on the inpatient unit, with follow-up interventions and procedures (e.g., transfer to emergency department/hospital, longer-term psychiatric hold on the unit, or withdrawal and referrals for treatment) implemented as necessary.

#### Unblinding

2.3.8.

Participant and facilitator blinding are maintained only until the primary endpoint of 48 h post-dosing in the randomized phase, to facilitate scheduling of subsequent open-label dosing for participants assigned to placebo (see Section 2.3.10.1). Specifically, unblinding will occur at the start of the 48 h post-dosing integration visit, which will always occur after the 48 h post-dosing ratings and fMRI scan. Independent raters will remain blinded until after the one-week post-dosing ratings are completed, which will be past the primary endpoint, thus not impacting primary outcomes.

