##### Primary outcomes

2.4.1.1.

The primary outcome measures are the acute version of the clinician-administered Y-BOCS (AY-BOCS) (52) and the self-report Visual Analog Scale (VAS) for OCD symptoms (53), both of which assess OCD symptom severity over the past 24 h. These will be administered by independent raters at baseline and 24 and 48 h post-dosing. The Y-BOCS will also be administered by the same raters at baseline and 1, 2, 4, 8, and 12 weeks post-dosing.

Safety outcomes are included as primary outcomes as well. Safety measures assessed only during dosing include vitals and SUDs, and those assessed throughout the study duration include the Since Last Visit version of the C-SSRS (54), AEs, and any required changes to psychiatric or non-psychiatric medication regimens. The Since Last Visit version of the C-SSRS (54) assesses suicidal ideation severity, ideation intensity, and suicidal behavior severity (including non-suicidal, self-injurious behaviors) since the last assessment interval (i.e., the last study visit). AEs are defined as any untoward physical, social, economic, or psychological occurrence affecting participants, including any abnormal laboratory finding, symptom, reaction, or disease. An AE does not necessarily have a causal relationship with study procedures, and are graded as mild, moderate, or severe in this study. Severity of an AE is considered distinct from its “seriousness.” An AE is considered serious (i.e., SAE) if it: (1) is life-threatening; (2) results in hospitalization, disability/incapacity, a congenital anomaly or birth defect, or death; (3) requires medical or surgical intervention to prevent aforementioned outcomes; or (4) adversely affects the risk/benefit ratio of the study. Therefore, a severe AE is not necessarily an SAE.

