### Statistical analysis

2.9.

We will conduct linear mixed modeling (LMM) with restricted maximum likelihood estimation (to handle missing data) with appropriate alpha correction in SPSS to test our first hypothesis that psilocybin, compared to placebo, will improve OCD symptoms at the primary endpoint of 48 h post-dosing on the VAS for OCD symptoms and AY-BOCS. Treatment, time, and all interactions will be modeled as fixed effects. Participants will be modeled as a random effect. The time factor will be specified as baseline to 48 h post-dosing. Alpha-corrected *t*-tests will be used to probe interaction effects.

MRI preprocessing and group difference statistics will be evaluated using standard regression and general linear modeling approaches in a general-purpose MRI analysis package (QuNex), a processing platform that incorporates several state-of-the art neuroimaging tools (FSL, FreeSurfer, AFNI, SPM, PALM, and HCP-MPP) and thus offers comprehensive multimodal MRI analytic capabilities (92). To test the secondary hypothesis that at 48 h post-dosing, psilocybin, compared to placebo, will normalize frontostriatal connectivity at rest, we will conduct similar LMMs to examine the effect of psilocybin on activation of the corresponding regions. To test the secondary hypothesis that normalization of activity in these regions at 48 h post-dosing will correlate with clinical improvement in OCD symptoms (i.e., on the VAS for OCD symptoms, AY-BOCS, and Y-BOCS), we will conduct a correlational analysis with these variables.

Exploratory analyses of change in other secondary outcomes from baseline to 48 h post-dosing will be conducted using similar LMMs. Safety data will be presented as descriptive statistics. Data from the one-month post-dosing interviews will be qualitatively analyzed *via* interpretative phenomenological analysis (IPA) (93).

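### The planned correlation of 48 h connectivity change with Y-BOCS improvement can only use Y-BOCS ratings taken after participants have been told their arm

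*Protocol article*

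**What the plan says.** All references are to the protocol article.

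- **When the blind ends (2.3.8 Unblinding).** "Participant and facilitator blinding are maintained only until the primary endpoint". For these two groups, "unblinding will occur at the start of the 48 h post-dosing integration visit", a visit "which will always occur after the 48 h post-dosing ratings and fMRI scan". The reason given is the scheduling of open-label dosing for the placebo arm. For raters: "Independent raters will remain blinded until after the one-week post-dosing ratings are completed". The section adds that this point is one "which will be past the primary endpoint, thus not impacting primary outcomes".
- **What is rated when (2.4.1.1 Primary outcomes).** The two named primary symptom measures, AY-BOCS and VAS, are taken at baseline, 24 h and 48 h. "The Y-BOCS will also be administered by the same raters", at baseline and at weeks 1, 2, 4, 8 and 12.
- **What is tested (2.9 Statistical analysis).** The primary mixed model runs from baseline to 48 h on the VAS and AY-BOCS. A secondary hypothesis correlates 48 h normalization in the frontostriatal regions with clinical improvement "on the VAS for OCD symptoms, AY-BOCS, and Y-BOCS".
- **Open-label phase (2.3.10.1).** Placebo participants may receive psilocybin about 2 weeks after unblinding.

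**The concern.** Three measures are listed side by side for one test, but they do not have the same standing. The AY-BOCS and VAS are rated at 48 h, close to the scan and before disclosure. The Y-BOCS is not rated at 48 h at all. Section 1.2 frames the connectivity-symptom hypothesis at 48 h, so the Y-BOCS limb does not match its time point.

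The Y-BOCS is clinician-administered, but the score rests on what the participant reports. Someone told that they received placebo may report less improvement, and someone told that they received psilocybin may report more, without any further drug effect. A blind rater at week 1 cannot remove that. Extending the rater blind to week 1 could therefore lead readers to take the 1-week Y-BOCS as a masked result when it is not.

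At stake is how the Y-BOCS limb of a secondary mechanistic test is read, and how any between-arm Y-BOCS result from week 1 onward is described.

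**Working it through.** The plan states no figure for this point, so there is none to reproduce. The main check is a timeline; a short calculation then bounds the effect on the correlation.

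**Step 1. Set each post-dose rating against the blind.** Days are counted from blinded dosing. Participant unblinding is at day 2. Open-label dosing, where taken, is at about 2 + 14 = day 16.

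| Rating | Day | Participant knows arm? | Rater blind planned? | After open-label psilocybin (placebo participants who take it)? |
|---|---|---|---|---|
| AY-BOCS, VAS 24 h | 1 | No | Yes | No |
| AY-BOCS, VAS 48 h | 2 | No | Yes | No |
| Y-BOCS week 1 | 7 | Yes | Yes | No |
| Y-BOCS week 2 | 14 | Yes | Ended | No, at the approximate timing stated |
| Y-BOCS week 4 | 28 | Yes | Ended | Yes |
| Y-BOCS week 8 | 56 | Yes | Ended | Yes |
| Y-BOCS week 12 | 84 | Yes | Ended | Yes |

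Five of five post-dose Y-BOCS ratings follow participant unblinding. The rater blind covers one of the five. For placebo participants who take open-label dosing, three of the five also follow psilocybin. The earliest Y-BOCS falls 7 − 2 = 5 days after the scan.

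**Step 2. How knowledge of arm could enter the correlation.** The scan comes before unblinding, so being told the arm cannot change connectivity. It can act only on the Y-BOCS side. If the correlation is run within the psilocybin arm, everyone has been told the same thing and disclosure cannot separate participants by arm. If the arms are pooled, a correlation arises when both variables differ by arm.

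**Step 3. How large that could be.** Take equal arms, within-arm SD of 1 for both variables and no within-arm correlation. Let *a* be the arm difference in connectivity change and *b* the arm difference in Y-BOCS improvement due only to knowledge of arm. Then

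r = (ab/4) / √[(1 + a²/4)(1 + b²/4)].

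Section 2.2 cites connectivity effects of d = 0.2 to 0.3 in healthy controls and speculates that they may be larger in patients. The documents give nothing for *b*, so the values below are assumptions, as is a = 1.0.

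- a = 0, any b: r = 0.
- a = 0.2, b = 0.5: 0.025 / √(1.01 × 1.0625) = 0.025 / 1.036 = 0.02.
- a = 0.3, b = 1.0: 0.075 / √(1.0225 × 1.25) = 0.075 / 1.131 = 0.07.
- a = 1.0, b = 1.0: 0.25 / 1.25 = 0.20.

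The induced correlation is nil without an arm difference in connectivity, small at the effect sizes the article cites, and about 0.2 if both differences reach 1 SD.

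**The case against.** The strongest case is that this is a disclosed trade-off. Section 2.3.8 gives a reason for unblinding participants at 48 h, and it ensures that the 48 h ratings and scan come first. The Y-BOCS enters only a secondary correlation, and 2.2 calls the connectivity analyses largely exploratory. Section 2.9 names neither the Y-BOCS time point nor whether arms are pooled, and an article may leave both to the full plan. Sections 2.3.4 and 3 also concede that the blind is hard to keep, so only the increment from being told the arm is at issue.

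Most of this stands and limits the weight of the point. It does not remove it: whichever Y-BOCS time point the full plan names, the stated schedule places it after disclosure and after the scan.

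Four stronger readings are tempting, and the documents do not support them.

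- **That the primary result is compromised.** All AY-BOCS and VAS ratings precede unblinding.
- **That the Y-BOCS is a primary outcome.** It is described under that heading, but the measures named as primary are the AY-BOCS and VAS.
- **That a false-positive rate can be attached to a two-arm test of the 1-week Y-BOCS.** Section 2.9 plans no such test, and the size of the bias would have to be invented.
- **That raters should be masked through 12 weeks.** Rater masking adds little once participants know their arm. Only placebo participants repeat the assessment series after open-label dosing, so the schedule itself would reveal the arm to the same raters. Masking would need different raters or new logistics.

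**Conclusion.** The point holds as a limited one. The plan includes in a 48 h mechanistic test a measure that is not taken at 48 h and whose every post-dose value comes from a participant who knows the arm. The timeline part rests only on stated times and needs no assumption. The distortion of the correlation is conditional: it needs pooled arms and an arm difference in connectivity, and its size is unknown. The range of 0 to about 0.2 shows what the assumptions imply and is not an estimate for this trial.

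The other consequence is one of labelling. The trial has no reading on the full Y-BOCS taken before disclosure, although the acute version is rated under the blind at 24 h and 48 h. A blind rater at week 1 should not be presented as giving a masked Y-BOCS.

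**What to change.** **Main change, in 2.9.** Limit the test of the 48 h connectivity-symptom hypothesis to AY-BOCS and VAS change from baseline to 48 h. If a Y-BOCS correlation is still reported, name its time point and label it participant-unblinded and descriptive. Apply the same label to all between-arm Y-BOCS results from week 1 on, and note that for placebo participants who take open-label dosing, weeks 4 to 12 follow psilocybin. The cost is a few sentences. No data collection changes, because both retained measures are already rated at baseline and 48 h. The formal test loses one of its three symptom measures.

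**Optional change, in 2.3.8.** If the sponsor wants one between-arm Y-BOCS reading taken before arms are disclosed, unblind participants and facilitators after the 1-week Y-BOCS rating. This has a real cost: unblinding moves by about five days, the 48 h integration session is held under the blind, and open-label re-screening and scheduling, which the plan ties to unblinding, must move or be re-anchored. It recovers one of the five Y-BOCS time points. Whether that is worth the re-scheduling is for the sponsor to decide; the main change does not depend on it.
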